## Input and modification of data

Data entry and management by the Shanghai Tigermed Co. Ltd. (CRO) statistics department is responsible for, will designate special personnel data management, developing data management plan. To ensure the accuracy of the numerical data, using double entry and proofreading; adverse events and drug in combination with single input and manual check.

The present case report table in question, the data administrator will fill in question and answer form (DRQ), and send inquiries to the researchers through clinical research associate, researchers should answer as soon as possible and return the data administrator data modification according to the researcher's answer, confirmation and entry, when necessary, can be re issued DRQ.

## Data verification

The verification of the data will be divided into manual verification and system verification. Manual verification is the data administrator errors found by consistency, check the data logic and other means to produce DRQ. The system checks or procedural examination (Computerized edit check) refers to the verification, the data in the CRF by the method of the computer program including range, logic, consistency, scheme violated and deviation. The DRQ will be handed over to the CRA, the CRA to researchers to determine again. The amendment requires researchers to sign and date.

## Locking and unblinding of database

Confirmation and the blind review database correctly, by the main researchers, the applicant, statistical analysis of common database lock. Do not allow the database principle changes after locking. Find the data after lock problem, can be confirmed by the analysis program in statistical correction, and keeping a written record.

The data will be kept locked, the blind end of head of the unit staff, the applicant and the statistics personnel joint first exposing blind, to determine the order of A, B in which the group encoding each of the subjects belonging to, and make statistical analysis according to the statistics personnel database plan requirements for statistical analysis, and then the two open label, determine the trial group and control group. The statistical analysis report writing statistical units, mainly studies the test write research reports.

# Statistics

## Sample size estimation

This study is the research on high efficiency, the efficiency test of the main therapeutic effect index. A: bilateral α = 0.05, P = 0.20, the standard deviation of the difference between SD=7.8mmHg and D detected two groups of antihypertensive effect of = 3mmHg, two cases of the distribution ratio of 1:1, the estimated minimum sample size was 108, taking into account factors such as the research plan off, 260 cases into two groups, the experiment group and the control group with 130 cases in each. The estimation results of PASS2008 software sample:

**Numeric Results for Superiority Test (H0: D <= |E|; H1: D > |E|)**

**Test Statistic: T-Test**

|  |  | **Equivalence** | **Actual** | **Significance** |  | **Standard** | **Standard** |
| --- | --- | --- | --- | --- | --- | --- | --- |
|  |  | **Margin** | **Difference** | **Level** |  | **Deviation1** | **Deviation2** |
| **Power** | **N1/N2** | **(E)** | **(D)** | **(Alpha)** | **Beta** | **(SD1)** | **(SD2)** |
| 0.80229 | 108/108 | 0.00 | 3.00 | 0.02500 | 0.19771 | 7.80 | 7.80 |

## Definition and selection of analytic set

The full analysis set and statistical analysis conducted in accordance with the scheme set set and data security. The whole process of statistical data will be strict quality control to ensure the authenticity of the data, assessment.

Full analysis set (Full analysis set, FAS): according to the intention to treat (ITT) principle, the random into groups, and the subjects more than once medication administration record and to evaluate the effectiveness of the enrolled in the full analysis set. In the choice of full analysis set analysis, the missing value estimation, can adopt the LOCF (LOCF) estimation method. Full analysis set is the main evaluation of the effectiveness of the study population.

The project sets (Per-Protocol set PPS): with the scheme set includes all completed treatment provisions scheme or no serious violations of test subjects. The exact definition of serious violations of the scheme will ultimately determine the data audit, generally include the following situations (but are not limited to these cases): Do not meet the criteria, interference treatment in selected, poor compliance, and visit beyond the time window. PP set is a secondary analysis of the crowd's effectiveness, but the results such as the full analysis set is inconsistent, to the detailed analysis of the inconsistent results.

Safety data set (Safety Set, SS): the definition of safety data set for at least the subjects received a drug treatment.

## Hypothesis testing

Superiority test primary efficacy index:

***H*0:μtreatment-μplacebo≤0**

***H*1:μtreatment-μplacebo＞0**

**α=0.05(two setting)**

**μtreatment-μplacebo**

**u= Se ＞1.96**

The alpha level to H0, lower or test group and placebo hypotensive effect difference of 95%CI is greater than 0, it is considered that the experimental group is better than the placebo.

All other statistical tests using bilateral test P value of less than or equal to 0.05 can be considered statistically significant.

## Statistical methods

### Aalysis method

Statistical analysis using SAS9.13 statistical analysis software for calculation. Quantitative description of the calculation of mean and standard deviation, median, minimum value, maximum value. Classification index described by number and percentage of cases.

Completion of the study will be carried out descriptive statistics on the demographics and baseline characteristics were compared between the two groups in a balanced analysis between groups.

Analysis of the main outcome measures: the main efficacy index will adopt non inferiority test. In addition, also calculate each subject after 8 weeks of treatment, DBP decreased and the seat value groups (mean standard deviation, median, minimum and maximum), groups were compared using analysis of variance center effect considered.

Analysis of secondary efficacy indicators: in principle does not consider the center effect, by using variance analysis, chi square test or nonparametric statistical method for comparison between groups.

Analysis of safety evaluation, safety evaluation included adverse events / ADR / important adverse events or serious adverse events, physical examination and laboratory examination and a 12 lead electrocardiogram. Cases of adverse events during the detailed description of test, summary comparison of incidence of adverse events between the two groups. Statistical description and index of laboratory examination and necessary changes were compared between the two groups. A detailed description of laboratory indexes was normal before treatment after treatment of abnormal.

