| **Statistical analysis** | **Estimation of sample sizes:**  This is a superior efficacy test study. The efficiency test was conducted on the main therapeutic effect index. Setting bilateral α = 0.05, *β* = 0.20, and the standard deviation SD = 7.8 mmHg, the difference of the antihypertensive effect in the two groups were detected as *D* = 3 mmHg. The distribution ratio of the patient cases in the two groups was 1:1. The estimated minimum sample size was 108 pairs. Taking into account of the factors such as dropping, the present research plan included 260 cases into the two groups with 130 cases of patients in the experiment group and the control group, respectively.  **Statistical analysis of the data set:**  Statistical analysis was conducted by using the full analysis set, per-protocol population set and safety data set. The quality control was strictly carried out in the whole process of the data statistics to ensure the authenticity of the assessment of data.  Full analysis set (Full analysis set, FAS): according to the fundamental principle of intention to treat (ITT), all the randomly enrolled subjects with more than one medication administration record and effective evaluation were included in the full analysis set. When selecting full analysis set for analysis, the latest observation LOCF (LOCF) estimation method was adopted for the estimation of the missing values. Full analysis set is the main effectiveness method for the evaluation of population in the present study.  The Per-Protocol set (PPS): PPS included all the subjects with completed prescribed treatment protocal or no serious violations of tests. The exact definition of the serious violations of the scheme will ultimately determined in the data auditing, which generally included the following situations (but they are not limited to these cases): Not meeting the inclusion criteria, having interference treatment after being selected, poor compliance, interview beyond the time window. PP set is a secondary analysis of the crowds of the effectiveness, but if the results were inconsistent with the full analysis set, detailed analysis should be done on the inconsistent results.  Safety data set (Safety Set, SS): the definition of safety data set was the subjects that at least received one time drug treatment.  **Statistical analysis method:**  Statistical analysis was conducted by using the SAS9.13 statistical analysis software for calculation. Quantitative description of the parameters included the calculation of mean, standard deviation, median, minimum value and maximum value. The description of the classified index employed the case number and percentage of the cases.  Descriptive statistics were conducted on the completion of the study. The comparison among groups was conducted on the demographic and baseline characteristics to analyze the equilibrium between groups.  Analysis of the main outcome measures: the main efficacy index will use the test of superiority. In addition, the dereasee value os DBP of each subject after treatment of 8 weeks will also be calculated, and descriptions in each group were done (mean, standard deviation, median, minimum, maximum). Comparisons between groups used analysis of variance considering center effect.  Analysis of the secondary outcome indicators: the center effect was not considered in principle. Comparisons between groups employed the variance analysis, chi-square test or nonparametric statistical method.  Analysis of the safety evaluation: parameters of safety evaluation included adverse events/ adverse drug reaction (ADR)/important adverse events or serious adverse events, physical examination and laboratory examination and a 12-lead electrocardiogram. Detailed description was conducted on the cases of adverse events during the test. The incidence rates of the adverse events between the two groups were summarized and compared. The indexes of laboratory examination were statistically described. The difference between two groups was compared when it was necessary. A detailed description of the laboratory indexes and normal cases before treatments was conducted.  This study did not conduct interim analysis. |

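### Section 11.4.1 names a non-inferiority test against placebo for the primary endpoint, while the rest of the protocol specifies superiority

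*Protocol*

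**What the plan says.** Section 11.4.1 (Analysis method) says of the primary endpoint that "the main efficacy index will adopt non inferiority test". It gives no margin, and none appears elsewhere in the Protocol. The comparator is placebo.

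The other places that describe the primary test say something different:

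- The Protocol summary, in the same position in its analysis text, says "the main efficacy index will use the test of superiority". Its sample size paragraph opens with "This is a superior efficacy test study".
- Section 11.1 shows software output headed "Numeric Results for Superiority Test", with margin 0.00, difference 3.00 mmHg, significance level 0.025, SD 7.80 in both arms, 108 per arm and power 0.80229.
- Section 11.3 (Hypothesis testing) opens with "Superiority test primary efficacy index". It sets the null hypothesis as treatment minus placebo at or below zero and uses a critical value of 1.96. On its success criterion it says: "hypotensive effect difference of 95%CI is greater than 0, it is considered that the experimental group is better than the placebo".
- Section 2.1 gives the primary objective as confirming the absolute blood-pressure-lowering effect of the 240 mg tablet in comparison with placebo.

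**The concern.** The section a programmer or SAP author would follow for the primary analysis names a different kind of test from the one the trial was designed and sized for.

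Non-inferiority to an active control can support efficacy, because the control is known to work. Non-inferiority to placebo cannot do so for any margin above zero, because a drug with no effect, or a slightly harmful one, satisfies the claim.

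The conflict also leaves room for argument after unblinding. Every result that passes superiority also passes non-inferiority with a positive margin. A sponsor free to invoke either wording would therefore have the false-positive rate of the weaker test, and since no margin is fixed, that rate has no stated limit.

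**Working it through.** **1. The plan's own figure.** The inputs come from the output in 11.1: difference 3 mmHg, SD 7.8 mmHg, margin 0, one-sided alpha 0.025 (the two-sided 0.05 of the text), 108 per arm.

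- SE of the difference = 7.8 × √(2/108) = 1.061 mmHg.
- Normal approximation: power = Φ(3/1.061 − 1.96) = Φ(0.866) = 0.807. The smallest size for 80% power is 107 per arm.
- t-test (noncentral t, 214 df): power = 0.803 at 108 per arm and 0.7997 at 107, so 108 is the smallest size reaching 80%. The plan states 0.80229.
- A one-sided alpha of 0.05 would need only 84 per arm, so that reading is ruled out.

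The stated size is therefore that of a superiority t-test with margin zero. The arithmetic alone would fit a 3 mmHg margin with a true difference of zero equally well, but the output states margin 0.00 and difference 3.00, which settles the reading.

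**2. What 11.4.1 would mean if taken literally.** The Protocol gives no margin M, so a range is assumed here. Differences are DBP reduction on drug minus DBP reduction on placebo.

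- Chance that a drug with zero effect succeeds: Φ(M/SE − 1.96).
- Smallest observed difference that succeeds: 1.971 × 1.061 − M = 2.09 − M, where 1.971 is the t critical value on 214 df.

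| Assumed margin (mmHg) | M/SE − 1.96 | False success, normal | False success, t-test | Smallest observed difference that passes (mmHg) |
|---|---|---|---|---|
| 0 (rule in 11.3) | −1.960 | 2.5% | 2.5% | 2.09 |
| 1 | −1.018 | 15% | 15.3% | 1.09 |
| 1.5 | −0.547 | 29% | 29.0% | 0.59 |
| 2 | −0.076 | 47% | 46.6% | 0.09 |
| 3 | 0.866 | 81% | 80.3% | −0.91 |

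In the last row an observed result 0.91 mmHg worse than placebo would still count as success. The 80.3% equals the design power because the margin of 3 takes the place of the design difference of 3.

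**3. After correction.** With superiority in 11.4.1 the design stays at 108 per arm, power 0.803 by the t-test, and a one-sided type I error of 2.5% at a true difference of zero.

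**The case against.** The strongest reply is that the Protocol contains only one complete decision rule, the one in 11.3. Section 11.4.1 supplies no hypotheses, margin, critical value or interval criterion, so it cannot be run as a rival. The only margin stated anywhere is zero, and at a margin of zero a non-inferiority test is the superiority test. The translation is visibly poor nearby: the prose of 11.1 loses the word superiority altogether, and Section 5.1 calls the trial phase I. With the Protocol summary carrying the same sentence correctly, intent is hardly in doubt. The error rates above rest on margins the Protocol does not contain. Exploiting the wording later would mean inventing a margin in the face of written hypotheses, a blind review, a database lock and an analysis plan (Section 10.6).

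Much of this stands. It probably is a slip, the error rates are illustrations and not properties of a planned test, and the statement that the test cannot show efficacy must be limited to margins above zero. None of it removes the contradiction. Section 11.4.1 does not say the margin is zero, and the Protocol sets no order of precedence between 11.3 and 11.4.1. A SAP written from one section would contradict the other. A term as specific as non-inferiority cannot be dismissed as loose English when it names the primary test.

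**Conclusion.** The concern holds: the primary test is wrongly named in 11.4.1. The contradiction itself rests on the text alone and needs no assumption.

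The size of the consequence does need one. For assumed margins of 1 to 3 mmHg, with SD 7.8 mmHg and 108 evaluable patients per arm, an inactive drug would pass between 15% and about 80% of the time, against 2.5% under 11.3. The design, sample size and hypotheses in 11.1 and 11.3 are consistent with each other and are not in question. Because the error concerns the trial's primary test, it should be corrected before the analysis is fixed, even though the likely cause is trivial.

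**What to change.** In Section 11.4.1 replace the reference to non-inferiority with the superiority test of 11.3: the null hypothesis is rejected if the lower limit of the two-sided 95% confidence interval for DBP reduction on treatment minus DBP reduction on placebo, at week 8, lies above zero. Add that this is the only confirmatory test, so that no second reading can be argued.

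One related point can be settled in the same edit. Section 11.3 writes a simple u statistic, while 11.4.1 goes on to name an analysis of variance with centre effect. The corrected sentence is the natural place to say which of them supplies the interval.

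The cost is a one-line protocol correction. The sample size, power and trial conduct are unaffected.

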# Efficacy assessment

## Primary outcome

- The changes from baseline in trough mean seated DBP (23 to 26 hours after the morning dose) to the end of the 8-week double-blind treatment period.

Baseline refers to the sitting blood pressure before giving the research drug in the randomized double-blind treatment period and after 2 weeks cleaning period.

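### The primary ANOVA of 8-week DBP change adjusts for centre but not for baseline DBP: valid, but it gives up precision that costs nothing to gain

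*Protocol*

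**What the plan says.** The primary endpoint (section 8.1) is the change in trough mean seated DBP from baseline to the end of the 8-week double-blind period. The same section defines the starting value: "Baseline refers to the sitting blood pressure before giving the research drug in the randomized double-blind treatment period", taken after the two-week placebo washout. Section 5.3.2 schedules that measurement at the baseline visit, where eligibility is confirmed and the random number assigned. Section 4.1 requires the post-washout DBP to be at least 90 and below 110 mmHg.

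The model is stated twice. Section 11.4.1 says "groups were compared using analysis of variance center effect considered"; the Protocol summary says "Comparisons between groups used analysis of variance considering center effect". Neither names baseline DBP, and nor does any other part of the protocol.

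Section 11.3 gives the decision rule: a superiority hypothesis with u = difference/Se above 1.96, or, on the confidence-interval version, "hypotensive effect difference of 95%CI is greater than 0, it is considered that the experimental group is better than the placebo". Se is not defined.

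The type of test is labelled inconsistently. Section 11.4.1 reads "the main efficacy index will adopt non inferiority test. In addition, also calculate each subject after 8 weeks of treatment", while the Protocol summary reads "the main efficacy index will use the test of superiority". The sample-size output in section 11.1 and the hypotheses in section 11.3 are also for superiority.

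**The concern.** Baseline DBP is the obvious covariate for a change in DBP. Subjects are selected on the same post-washout reading that is later subtracted, so subjects with higher baseline readings would be expected to show larger falls through regression to the mean. A model with treatment and centre only leaves that predictable variation in the residual, and any chance difference in baseline DBP between the arms passes into the estimate. Because the protocol names the model, the omission is part of what it fixes and not merely a detail left open.

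At stake are a wider confidence interval and some lost power. Separately, the success rule in section 11.3 does not say which model supplies its standard error.

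**Working it through.** **Inputs from the protocol (sections 11.1 and 11.3).** Difference D = 3 mmHg; SD = 7.8 mmHg in each arm; two-sided alpha 0.05 (one-sided 0.025 in the software output); 108 evaluable per arm; two-sample t-test; stated power 0.80229.

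**Reproducing the stated figure.** The noncentrality parameter is D / (SD × √(2/n)) = 3 / (7.8 × √(2/108)) = 2.83. The noncentral t distribution with 214 degrees of freedom gives power 0.803. At 107 per arm power is 0.7997, so 108 is the smallest n that reaches 80%. The design is adequately powered on its own assumptions without any baseline term.

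**Input not in the protocol.** The correlation r between baseline DBP and DBP change is assumed, with a range shown.

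**Effect of adding baseline.** Residual SD = 7.8 × √(1 − r²). For r = 0.3 this is 7.8 × √0.91 = 7.44. Power then follows as above, with one fewer degree of freedom (213):

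| Assumed r | Residual SD (mmHg) | Power at 108 per arm | n per arm for 80% power |
| --- | --- | --- | --- |
| 0 | 7.80 | 0.803 | 108 |
| 0.1 | 7.76 | 0.807 | 107 |
| 0.2 | 7.64 | 0.819 | 103 |
| 0.3 | 7.44 | 0.839 | 98 |
| 0.4 | 7.15 | 0.867 | 91 |
| 0.5 | 6.75 | 0.901 | 81 |

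The centre terms make almost no difference: with 8 centres and 207 degrees of freedom, power at r = 0 is still 0.803.

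**Which part of the range is plausible.** The entry window of 90 to below 110 mmHg limits the spread of baseline DBP, and so limits r. Let b be the size of the slope of change on baseline; then r = b × SD(baseline) / 7.8. Assuming a baseline SD of 4 to 6 mmHg and b of 0.2 to 0.6, r runs from 0.2 × 4 / 7.8 = 0.10 to 0.6 × 6 / 7.8 = 0.46. Power at 108 per arm is then about 0.81 to 0.89, a gain of less than 1 up to about 8 percentage points.

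**The case against.** The strongest objection is that nothing here is wrong. ANOVA of change with centre is a valid, unbiased comparison in a randomised trial. Regression to the mean acts on both arms alike and does not bias the difference. The stated power reproduces. An SAP that is not shown might also add covariates. Most of this stands: the point is about efficiency. It survives because the protocol does name the primary model, in two places, and leaves baseline out of both.

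A reader might infer three stronger things, which the document does not support.

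- **That the u-test in section 11.3 is unadjusted.** Se is undefined and could be the ANOVA's own standard error. The t-test in section 11.1 hints at an unadjusted test but concerns sample size only.
- **That omitting baseline leaves two competing primary results.** In the Protocol summary, the phrase meaning additionally introduces the calculation and description of each subject's DBP decrease, and the ANOVA has its own sentence. Section 11.3 can be read as the criterion and section 11.4.1 as the model. If there were two tests, the cause would be the lack of a stated hierarchy and not the missing covariate. The effect would also be small. In simulations with 8 centres of 27, and an assumed 0 to 10% of variance due to centre, an unadjusted u-test and the centre ANOVA disagreed in about 1.0 to 2.5% of trials at D = 3 and 0.1 to 0.5% under the null. The one-sided error of accepting either was about 0.022 to 0.029.
- **That adjustment is needed to repair a shortfall after 20% loss.** Taking 20% from 260 leaves 208, or 104 per arm, with power 0.788. But the primary set is the FAS with LOCF. In the earlier phase II trial, 279 of 283 randomised subjects entered the FAS. At that rate 130 × 279/283 ≈ 128 per arm would be analysed, with power about 0.865 without a baseline term.

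**Conclusion.** The point holds as a free improvement. Both statements of the primary model omit a covariate that is defined, scheduled before treatment and measured on everyone. Including it would raise power at 108 per arm from 0.80 to between 0.81 and 0.90 for an assumed correlation of 0.1 to 0.5. At the low end the gain is negligible (0.803 to 0.807). These figures rest on the protocol's D and SD, a linear relation between baseline and change with the same slope in both arms, and a correlation the document does not give.

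The omission makes the trial neither biased nor underpowered against its own assumptions. Two wording defects beside it are plain on the page: Se is undefined in the decision rule, and section 11.4.1 calls the primary test non-inferiority where the Protocol summary and sections 11.1 and 11.3 specify superiority.

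**What to change.** In section 11.4.1 and the Protocol summary, define the primary analysis as an ANCOVA of week-8 DBP change with terms for treatment, centre and baseline DBP. In section 11.3, state that the treatment difference, its standard error and the 95% CI used in the superiority rule come from that model. In section 11.4.1, replace the non-inferiority label with superiority.

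The same model, with each variable's own baseline, can be used for the secondary changes in DBP at week 4 and SBP at weeks 4 and 8.

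The cost is analysis wording only. No new data, visits or subjects are needed, and the sample size can stay as it is.

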# The expected duration of research, the number of research center and of the case number of planning

The present research program is planned to enroll subjects from May of 2009, and finish grouping in August of 2009, and statistical analysis and summary will be conducted in December of 2009.

Research will be carried out in 8 National Research center. The study designs 1 treatment group and 1 placebo group. One hundred and eight cases of patients in each group can be evaluated, so a total of 216 cases of patients are needed to be evaluated. Considering a shedding rate of 20%, a total of 260 qualified cases of subjects with hypertension are needed to be enrolled.

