### Rules of breaking blinding of the randomized double-blind trial

**1）Blinding and preservation of blinding sheet**

Package of software was analyzed in computer by the biostatistician independent of the implementation of the data management and statistical analysis in the present study by using the SAS 9.13. The random encoding was produced by using the stochastic approach in the experiment group and the control group according to a ratio of 1:1. The length of the selected block and the initial seed parameters of the random number were sealed in the bottom of the blind area together as confidential data. The drugs were encoded according to thses random number under the surveillance of the personnel unrelated to the present test. The drugs were used by various clinical research centers according to the distributed number of the drugs and the grouping sequence of the cases. The blind end of two copies were sealed and stored in the sponsor’s department and the national drug clinical trial institution Office, the Third Xiangya Hospital of Central South University, the blind end should not be opened during the test.

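### Secondary efficacy comparisons by default leave out centre, which the primary analysis includes; if centres differ in blood pressure change, this costs some precision that could be recovered for free

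*Protocol*

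**What the plan says.** - **Secondary endpoints.** Section 11.4.1 says the analysis "in principle does not consider the center effect, by using variance analysis, chi square test or nonparametric statistical method for comparison between groups". The Statistical analysis row of the Protocol summary gives the same rule: "Analysis of the secondary outcome indicators: the center effect was not considered in principle".
- **Primary endpoint.** For the week-8 diastolic change the summary says "Comparisons between groups used analysis of variance considering center effect", and section 11.4.1 agrees.
- **Which endpoints the rule covers.** Section 8.2 lists the week-4 diastolic change, the week-4 and week-8 systolic changes, the effective rate at weeks 4 and 8, and the blood pressure changes among effective patients. Section 11.3 tests everything other than the primary endpoint two-sided at 0.05.
- **Allocation.** Section 5.2.2 describes a computer-generated 1:1 list: "The length of the selected block and the initial seed parameters of the random number were sealed". It adds: "The drugs were used by various clinical research centers according to the distributed number of the drugs and the grouping sequence of the cases". It states neither stratification by centre nor that each centre receives whole blocks.
- **Centres.** Section 3: "Research will be carried out in 8 National Research center".

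**The concern.** The same variable in the same patients, trough seated diastolic change, is modelled with centre at week 8 and by default without it at week 4. Systolic change is modelled without centre at both visits. The protocol gives no reason for the split.

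When allocation is roughly balanced within centre, leaving centre out moves any between-centre variance in the outcome into the error term. The treatment estimate hardly moves, but its reported standard error is larger than it needs to be, its interval wider, and its test rejects less often than the nominal 5% under the null. At stake is precision on the secondary endpoints, not their validity.

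**Working it through.** **1. The plan's own figure.** Section 11.1 gives a difference of 3 mmHg, SD 7.8 mmHg, two-sided alpha 0.05 (shown as one-sided 0.025 in the software output), 108 per arm and power 0.80229. The normal approximation, n = 2(1.960 + 0.842)² × 7.8² / 3², gives 107 per arm after rounding up. The noncentral t at 108 per arm gives power 0.803. The stated figure is reproduced.

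**2. Inputs for the comparison.**
- 130 per arm and eight centres, from the protocol.
- SD 7.8 mmHg, the planning value for the primary diastolic endpoint, used here as an illustration for the secondary changes.
- The share ρ of the variance of change that lies between centres. The protocol gives no value, so a range is assumed.

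**3. Formulas, with arms balanced within centre.**
- Without centre: SE = 7.8 × √(2/130) = 0.967 mmHg.
- With centre: SE = 7.8 × √(1 − ρ) × √(2/130), on 7 fewer degrees of freedom.
- Excess from leaving centre out: 1/√(1 − ρ) − 1.

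| Assumed ρ | SE without centre | SE with centre | Excess | 95% CI half-width without / with |
|---|---|---|---|---|
| 0 | 0.967 | 0.967 | 0% | 1.905 / 1.905 |
| 0.01 | 0.967 | 0.963 | 0.5% | 1.905 / 1.896 |
| 0.02 | 0.967 | 0.958 | 1.0% | 1.905 / 1.886 |
| 0.05 | 0.967 | 0.943 | 2.6% | 1.905 / 1.857 |
| 0.10 | 0.967 | 0.918 | 5.4% | 1.905 / 1.808 |
| 0.20 | 0.967 | 0.865 | 11.8% | 1.905 / 1.704 |

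The excess does not depend on the SD or on the number per arm. The first row shows that the lost degrees of freedom have no visible cost.

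**4. Simulation.** Assumed layout: 256 patients, eight equal centres, blocks of four within centre, 6,000 runs per setting.

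| Assumed ρ | Type I error without / with centre | Power at 3 mmHg without / with centre |
|---|---|---|
| 0 | 0.053 / 0.053 | 0.867 / 0.867 |
| 0.02 | 0.045 / 0.048 | 0.872 / 0.876 |
| 0.05 | 0.044 / 0.050 | 0.872 / 0.878 |
| 0.10 | 0.041 / 0.050 | 0.883 / 0.903 |
| 0.20 | 0.033 / 0.055 | 0.897 / 0.927 |

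The Monte Carlo standard error of a 5% rate is √(0.05 × 0.95/6000) = 0.003, so the values with centre are compatible with 5%. A second simulation used 260 patients, eight unequal centres of 16 to 50 patients and 4,000 runs. Including centre cut the SE by 2.1% at ρ = 0.05 and by 4.4% at ρ = 0.10, in line with the table.

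**5. Effective rate, on the risk-difference scale.** Take 58.33% on treatment (the 240 mg group at week 8 in the earlier phase II study, Research background) and an assumed 40% on placebo. Then SE = √(0.5833 × 0.4167/130 + 0.40 × 0.60/130) = 0.0610. Multiplying by √(1 − ρ) gives 0.0594 at ρ = 0.05 and 0.0578 at ρ = 0.10. This treats centre as explaining a share ρ of the binary variance. It does not carry over to an odds ratio: a centre-adjusted odds ratio is a different estimand, and its SE need not be smaller.

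**The case against.** The strongest reply is that nothing here is wrong. A comparison of randomised groups without centre is valid, the two statements of the rule agree, and the earlier phase II study used the same rule. This stands: the point is an available improvement, not an error.

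Several stronger readings are tempting, and the protocol does not support them.

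- **That the standard errors are certainly too large.** This depends on a between-centre variance that the protocol does not give. At a share of 1–2% the excess is at most about 1%.
- **That separate observers and mercury manometers make centre effects on change likely.** Appendix 2 prescribes one standard method, averaged readings, and the same time, arm, gauge and person. A constant observer or device offset also cancels in a change from baseline. Centre differences in change remain possible but cannot be presumed.
- **That week-4 and week-8 results, or diastolic and systolic results, could differ because of the model and not the drug.** If arms are near-balanced within centre, both models give nearly the same estimate, and only the standard error moves. No formal contrast of this kind is planned either.
- **That every secondary comparison ignores centre without exception.** The rule is qualified: "the center effect was not considered in principle". A statistical analysis plan may set exceptions. What can be judged here is the stated default.
- **That the allocation is stratified by centre.** Approximate balance is inferred from a blocked list used in order. The degree of conservatism in the simulations depends on the assumed whole blocks within centre.

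None of these replies shows a disadvantage of including centre. With no centre variance the cost is nil.

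**Conclusion.** The point holds as a conditional gain in precision. By default the secondary comparisons leave out a factor that the primary analysis includes and that allocation probably balances approximately. If centres differ in blood pressure change, the centre-free tests are conservative and their intervals slightly wide: the standard error is larger by nothing at a centre share of zero, about 0.5–1% at 1–2%, about 2.6% at 5% and about 5% at 10%. These shares are assumptions, and the figures also assume arms balanced within centre.

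There is no bias, no inflation of the type I error and no effect on the primary analysis. The conclusion covers the week-4 diastolic change, the week-4 and week-8 systolic changes, and the effective rate expressed as a risk difference. It does not cover blood pressure changes among effective patients. That subset is chosen by response after randomisation, so balance within centre is not assured there.

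**What to change.** In section 11.4.1 and the Statistical analysis row of the Protocol summary, replace the centre-free default with wording such as: *The week-4 DBP change and the week-4 and week-8 SBP changes are analysed in all FAS patients with the same model as the primary endpoint, including centre. The effective rate at weeks 4 and 8 is compared by a Cochran-Mantel-Haenszel test stratified by centre, with the common risk difference and its 95% confidence interval. Analyses without centre are supportive.*

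Blood pressure changes among effective patients should be kept out of this sentence and handled separately.

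The cost is a change of wording. Centre is already recorded and already in the primary model; no extra data or patients are needed.
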